### Data collection and statistical analysis

Two trained evaluators will collect baseline data, outcomes, and follow-up data. Participant trial data will be recorded through the case report form. Participants will be informed of follow-up visits after discharge from the hospital, and follow-up data will be obtained through telephone questionnaires or home visits. Two investigators will check the case report form twice to ensure accuracy and completion and record the data of the case report form into the Excel file with double-check.

All participants can withdraw from the trial at any time. If participants terminate the trial or deviate from the intervention protocol, the investigators will record the trial data from the participant’s last intervention and report the reason for withdrawal.

The SPSS 26.0 software (IBM SPSS, Chicago, IL) was applied to analyze the baseline characteristics and outcomes between the two groups. *x̅* ± s will represent continuous variables that conformed to the normal distribution, and the *t* test will compare the differences between the two groups. The Mann–Whitney *U* test will be applied if continuous variables are not normally distributed. Categorical variables will be expressed as frequency (percentage, %), and the chi-square test will be used to compare the differences between the two groups. Effect estimates will be provided with corresponding 95% confidence intervals, and *P* values ≤ 0.05 will be considered significant. Aiming to preserve the unique benefit of randomization, regardless of whether that participant received the allocated intervention, the principles of intention-to-treat analysis will be used. All randomized participants will be included in the analyses, and data will be analyzed in the group in which the participants were originally randomized. All available data from the NMES group that was originally randomized will be analyzed as an intervention group, including participants from the NMES group who do not complete the NMES intervention or even do not receive NMES intervention. Similarly, all available data from the control group that was originally randomized will be analyzed as the control group, including any who receive the NMES intervention. Multiple imputation (MI) using the mice package in R will be applied to analyze the missing data.

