## Introduction

Acute pancreatitis (AP) is a common disease in clinical practice due to an inflammatory disorder of the pancreas [1]. Twenty percent of AP patients may develop systemic inflammation leading to organ failure, defined as “severe acute pancreatitis (SAP)” [2–4]. Previous studies have demonstrated that the lung is the commonly damaged target organ caused by early induction of systemic inflammatory response syndrome (SIRS) in SAP [5]. One third of patients with severe pancreatitis develop acute lung injury (ALI) and ARDS in the first week [6], and these complications are responsible for high mortality and ICU admission [7–9]. In addition, blood purification, respiratory support, and sedation are common treatments but cause long-term bed rest for SAP patients with ARDS. Patients who stay in bed can experience muscle atrophy in the early stage. Studies have shown that the rectus femoris cross-sectional area decreases rapidly during the first week of bed rest; furthermore, muscle atrophy is more pronounced in patients with multiorgan failure [10, 11]. Muscle wasting is associated with reduced muscle strength and exercise capacity. The decline in exercise capacity is related to poor quality of life, increased mortality, and financial burden on healthcare [12–14]. Early intervention to reduce muscle wasting during the first week of bed rest in patients with SAP complicated with ARDS is urgently needed.

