## Method

### Study design

The overall objective of this trial is to explore the superior effects of NMES on preventing muscle wasting in patients with early SAP complicated with ARDS compared with sham intervention. We designed a randomized, prospective, single-blind trial (evaluator) because stimulation and contraction evoked during NMES therapy cannot be blinded to patients. Eighty patients who meet the inclusion criteria will be randomly divided into the NMES group and the control group at a ratio of 1:1. All participants will complete data collection and follow-up interviews. Assessment and treatment will be performed by a physician and therapist with 5 years of clinical experience, and diaphragm ultrasound evaluation will be performed by trained sonographers. Participants’ clinical assessments will be performed at baseline and 7 days postintervention, diaphragm ultrasound assessments will be performed daily, and follow-up assessments will be completed at months 1, 3, and 6 after discharge. The NMES group will receive neuromuscular electrical stimulation intervention and usual care for 7 days within 48 h of ICU admission, and the control group will receive the usual care only. The flowchart and study process are shown in Fig. 1 and Table 1, respectively.

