#### Primary outcome

##### MRC score

MRC score clinical assessments will be performed at baseline, and 7 days postintervention, MRC has proven to be a valid and reliable assessment scale to evaluate muscle weakness in critically ill individuals [30, 31]. MRC, as a convenient muscle strength assessment tool, is graded according to maximum muscle contraction, ranging from 0 to 5. The grade details are as follows: 0 = no contraction, 1 = visible and/or palpable contraction without limb movement, 2 = active movement, with gravity eliminated, 3 = active movement against gravity, 4 = active movement against gravity and submaximal resistance, and 5 = active movement against gravity and maximal resistance [32]. The MRC score was obtained by evaluating 6 groups of bilateral muscles. These include wrist dorsiflexors, elbow flexors, shoulder abductors, hip flexors, knee extensors, and ankle dorsiflexors. The total MRC score is 60, and higher MRC scores indicate better muscle strength [31].

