##### Diaphragm ultrasound

Diaphragm ultrasound assessments will be performed daily. The diaphragm thickness and thickening fraction will be measured by ultrasound (LOGIQ Book, GE Healthcare, Waukesha, Wisconsin, USA). For patients in supine positions, diaphragm assessment will be performed using M-ultrasound with a 6–12 MHz frequency ultrasound probe at the 8th to 10th intercostal space of the right midaxillary line. The distance between the pleura line and peritoneum line will be measured as the thickness of the diaphragm (tdi) at the end-expiration. The thickness of the diaphragm will be obtained by averaging the measurements over three breathing cycles. In addition, the thickening fraction will be calculated as ((tdi end-inspiration − tdi end-expiration)/tdi end-expiration) × 100%. A low-frequency convex transducer is placed below the costal margin of the midclavicular line and anterior axillary line. Then, diaphragmatic excursion of the right hemidiaphragm will be recorded during quiet breathing.

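### The rule for patients who stop or deviate from the intervention handles them as withdrawals, does not secure their day-7 MRC score, and conflicts with the intention-to-treat text

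*Protocol article*

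**What the plan says.** In the protocol's Data collection and statistical analysis section, the paragraph on withdrawal reads: "If participants terminate the trial or deviate from the intervention protocol, the investigators will record the trial data from the participant’s last intervention". The sentence ends by requiring that the reason for withdrawal be reported.

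The next paragraph of that section sets the analysis population: "All randomized participants will be included in the analyses, and data will be analyzed in the group in which the participants were originally randomized". It keeps all available data from the NMES arm, "including participants from the NMES group who do not complete the NMES intervention or even do not receive NMES intervention". On missing values it says: "Multiple imputation (MI) using the mice package in R will be applied to analyze the missing data".

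Study design states: "All participants will complete data collection and follow-up interviews". For the primary outcome, the MRC score section states: "MRC score clinical assessments will be performed at baseline, and 7 days postintervention" (called day 7 below). No MRC is scheduled in between. Of the outcomes, only the ultrasound is daily: "Diaphragm ultrasound assessments will be performed daily".

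**The concern.** Stopping a treatment and leaving a trial are different events. An intention-to-treat comparison needs the outcome at the planned time from everyone randomised, including those who stopped treatment. The quoted rule merges the two events, names the last intervention as the point of recording, and labels the result a withdrawal. It does not say that assessment continues.

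The primary outcome is at stake. If sites take the rule at its word, the day-7 MRC of patients who stop NMES may not be collected, and no later analysis plan can recover it. The patients affected are unlikely to be a random subset, because Safety assessment and monitoring provides for stopping NMES for discomfort. They are also likely to be concentrated in one arm. The interim analysis of the primary outcome at 40 participants would inherit the same gap.

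**Working it through.** The protocol gives no figure for this point: no rate of stopping NMES, and no MRC mean, SD or time course. The check is therefore mainly a reading of the text, followed by a conditional illustration.

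**1. The rule applied to each type of patient**

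- *Leaves the trial and withdraws consent to follow-up.* Keeping the data gathered so far and recording the reason is reasonable. The rule fits.
- *Stops NMES on day 3 but stays in the trial.* The rule points to the day-3 session. No MRC is scheduled then. The record holds an unscheduled MRC, only the baseline MRC, or no follow-up MRC. The intention-to-treat text and Study design both call for the day-7 value.
- *Randomised to NMES but never treated.* The intention-to-treat text expressly includes this patient. There is no last NMES session, so the rule cannot be applied.
- *Control patient who receives NMES.* This is also a deviation, and the same section keeps the patient in the control arm. The rule again points to a session, not to day 7.

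The rule fits only the first case. In the others it cannot be applied, or it differs from what the rest of the protocol asks for.

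**2. What each possible record does to the primary analysis**

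- An unscheduled early MRC, if analysed as day 7, compares the arms at different times.
- A baseline MRC, if analysed as day 7, does the same to a greater degree.
- A missing value goes to multiple imputation. That follows the stated method, but it models an outcome that could have been measured, partly from patients who may differ from those who stopped.

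**3. Illustration, valid only if the early value is used as the day-7 outcome**

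Assumptions, none of them from the protocol: a proportion *q* of the NMES arm stops, on average at day *t* = 3.5; MRC changes linearly by *C* points over 7 days in both arms; nobody in the control arm is affected.

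- Last-session value: bias = *q* × *C* × (7 − *t*)/7
- Baseline value: bias = *q* × *C*

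| *q* | *C* (points) | Last-session value | Baseline value |
|---|---|---|---|
| 0.20 | 5 | 0.20 × 5 × 0.5 = 0.5 | 0.20 × 5 = 1.0 |
| 0.20 | 10 | 0.20 × 10 × 0.5 = 1.0 | 0.20 × 10 = 2.0 |
| 0.30 | 5 | 0.30 × 5 × 0.5 = 0.75 | 0.30 × 5 = 1.5 |
| 0.30 | 10 | 0.30 × 10 × 0.5 = 1.5 | 0.30 × 10 = 3.0 |

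The sign follows the direction of change. If strength falls over the week, the NMES mean is overstated; if it rises, the NMES mean is understated; with no change there is no bias.

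A simulated t test (40 per arm, no treatment effect, 20,000 trials per setting) shows the effect on false positives. With a weekly change of 1 SD and stoppers valued halfway, the bias is 0.20 × 0.5 = 0.10 SD at 20% stopping, and the type I error is about 6.6 to 7.0%. At 30% the bias is 0.15 SD and the type I error about 9.7 to 10.0%. With a change of 0.5 SD and 20% stopping it is about 5.5%. With no change it stays at about 5%.

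**The case against.** The best defence is that the sentence is a recording rule and nothing more. It follows a statement that participants may withdraw at any time and ends by asking for the reason, so it can be read as applying to withdrawals: keep what was collected and say why. It does not cancel the day-7 assessment. No carry-forward method appears anywhere in the protocol. Multiple imputation is the stated method, intention-to-treat expressly includes patients who received no NMES, and Study design expects everyone to complete data collection. Because no MRC is scheduled between baseline and day 7, there is usually no last-session MRC to substitute.

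Much of this stands. A reader might infer that the plan replaces the day-7 MRC with an early value; the text does not say so. A reader might also infer that the 1-, 3- and 6-month Barthel is lost for patients who stop NMES. Follow-up is by telephone or home visit and nothing excludes them, so that too is inference. Nor is it shown that a bias would favour NMES. The Introduction says that "the rectus femoris cross-sectional area decreases rapidly during the first week of bed rest", but that is muscle size, not MRC score, and strength might rise during the week. Withdrawal can occur in both arms, and controls can deviate by receiving NMES, so the imbalance between arms is plausible but not quantified.

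The defence does not remove the wording itself. The sentence names deviation from the intervention alongside termination and calls the outcome withdrawal. The benign reading, in which last-session data are extra and day 7 is still collected, is possible but written nowhere. Inclusion criterion 4, which refers to completing the course of treatment, points the other way. This conflict lies within the document and concerns data collection, so a separate analysis plan could not repair it afterwards.

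**Conclusion.** The point holds as an internal conflict with a practical risk. The protocol handles a patient who only stops or deviates from NMES as a withdrawal, does not secure that patient's day-7 MRC, and so contradicts its own intention-to-treat and complete-data statements. The literal result is an off-schedule or baseline MRC, or an imputation that could have been avoided. The NMES arm is the more exposed, since only it has NMES sessions to stop.

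The point does not extend to a finding that the primary outcome is replaced by an early value. Any bias is conditional on that reading. Its direction depends on how strength moves during the week, and its size cannot be derived from the protocol. The figure of 0.5 to 1.0 MRC points (20% stopping at mid-week, 5 to 10 point change) and the type I error figures show only what would follow under the stated assumptions.

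**What to change.** Replace the sentence with wording such as:

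> Stopping or deviating from NMES is not withdrawal from the trial. Every randomised patient, whatever NMES was received, has the day-7 assessment and the 1-, 3- and 6-month Barthel unless consent to follow-up is withdrawn. The date, number of sessions and reason for stopping are recorded. Values from the last session are not used as day-7 outcomes, and day-7 values that are truly missing are handled by the planned multiple imputation.

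This changes no sample size and adds no assessment, because all of these are already planned for every participant. The cost is a protocol wording change and some assessor time for patients no longer on NMES. It should be made before further patients reach day 7, because a day-7 score that was not taken cannot be collected later.

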### Simple size

Campos DR et al. reported that the incidence of ICU-AW in the control group was P_1_ ≈ 0.45, and in the intervention group, it was P_2_ ≈ 0.11 [25]. According to those results, a sample size of 40 participants in each group was calculated to sufficiently detect the target effect size (0.5) with a type I error of 5% (*α* = 0.05) and 90% power (*β* = 0.10) by the PASS15.0 software. Allowing for a 20% loss to follow-up, this study was designed to include 80 cases.

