##### Barthel Index

Barthel Index assessment will be performed at baseline and 7 days postintervention, and Barthel Index follow-up data will be collected in the 1st month, 3rd month, and 6th month after discharge. The Barthel index is used to assess the recovery of daily life function in critically ill patients, and it values ten items (personal hygiene, bathing self, feeding, toilet, stair climbing, dressing, bowel control, bladder control, ambulation, chair/bed transfers), yielding a score of 0–100. A higher score is associated with a greater degree of independence in daily life.

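### All outcomes are compared by unadjusted two-group tests chosen on observed normality: valid, but baseline data already collected go unused and the repeated outcomes have no named contrast

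*Protocol article*

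**What the plan says.** The section Data collection and statistical analysis of the protocol article sets one set of methods "to analyze the baseline characteristics and outcomes between the two groups". For normally distributed variables a t "test will compare the differences between the two groups"; a Mann–Whitney "test will be applied if continuous variables are not normally distributed"; categorical variables get a chi-square test. Results at P ≤ 0.05 count as significant, and effect estimates come with 95% confidence intervals. The section adds intention-to-treat and multiple imputation. It names no covariate, no repeated-measures model and no multiplicity rule for secondary outcomes, and it does not say whether day-7 values or changes are compared.

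The outcome sections show what is collected:

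- Primary: "MRC score clinical assessments will be performed at baseline, and 7 days postintervention".
- Grip strength, thigh and calf circumference, APACHE II, modified Marshall and SOFA scores: also at baseline and day 7.
- Diaphragm thickness, thickening fraction and excursion: "Diaphragm ultrasound assessments will be performed daily".
- Barthel Index: baseline and day 7, after which "Barthel Index follow-up data will be collected in the 1st month, 3rd month, and 6th month after discharge".

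**The concern.** There are three linked weaknesses in a method that the article states outright.

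1. The baseline value of an outcome is often its best single predictor. Leaving it out of the comparison gives up precision and leaves any chance baseline imbalance in the estimate. With 80 patients, such imbalance is plausible.
2. Choosing between t and Mann–Whitney on the observed distribution means that the primary test, and the estimate that goes with it, are not settled until the data are seen.
3. A two-group test takes one value per patient. For the diaphragm measures and the Barthel Index the article does not say which value that is. The analyst could test every day or month, or pick one later. The question of a sustained effect, raised in the Discussion, then has no single pre-stated answer.

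**Working it through.** **The plan's own figure.** The section headed "Simple size" uses rates of 0.45 and 0.11, α = 0.05 and 90% power. Two-sided with unpooled variance:

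n = (0.45×0.55 + 0.11×0.89) × (1.960 + 1.282)² / 0.34² = 0.3454 × 10.507 / 0.1156 = 31.4, so 32 per group; 32/0.8 = 40 per group, 80 in total.

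The stated total therefore reproduces from the two rates. It tells us nothing about the precision of a comparison of MRC scores, which is the primary outcome.

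**Precision from baseline adjustment.** With baseline-to-outcome correlation r, ANCOVA multiplies the variance of the group difference by 1 − r². The confidence interval width is multiplied by √(1 − r²), and 80 adjusted patients carry the information of 80/(1 − r²) unadjusted ones. The values of r are assumptions.

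| r (assumed) | variance factor 1 − r² | variance reduction | interval width factor | 80 patients equivalent to |
|---|---|---|---|---|
| 0 | 1.00 | none | 1.00 | 80 |
| 0.3 | 0.91 | 9% | 0.95 | 88 |
| 0.5 | 0.75 | 25% | 0.87 | 107 |
| 0.7 | 0.51 | 49% | 0.71 | 157 |

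**Illustration in power.** The article states an effect size of 0.5 without a scale. Suppose, as an assumption, that it is a standardised mean difference. Power then comes from the noncentral t distribution with noncentrality [0.5/√(1 − r²)] × √(n/2), two-sided at 0.05 and ignoring the interim look:

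- 40 per group: 60% unadjusted; 64%, 72% and 87% at r = 0.3, 0.5 and 0.7.
- 32 per group (after 20% loss): 50% unadjusted; 54%, 62% and 79%.

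**Room for multiple tests.** Taking daily to mean the 7 intervention days, 3 diaphragm measures × 7 days = 21 possible comparisons. The Barthel Index has 4 post-baseline times. The chance of at least one false positive among the 21, each at 0.05, is:

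- All independent: 1 − 0.95²¹ = 66%. This is a ceiling, because daily readings in one patient are correlated.
- Days correlated at 0.5, 0.7 or 0.9 (assumed): simulation gives 23%, 18% or 11% for one measure over 7 days. With the three measures independent of one another: 1 − (1 − 0.230)³ = 54%, 1 − (1 − 0.179)³ = 45%, 1 − (1 − 0.114)³ = 30%.
- All 21 results correlated with one another at 0.5, 0.7 or 0.9: 43%, 29% or 16%.

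For the four Barthel times the figure is 19% if independent, and 15%, 13% or 9% at those same correlations.

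**The case against.** The best defence is that two-group tests are valid in a 1:1 randomised trial, and that covariates and longitudinal models are often left to a SAP or full protocol that is not shown here. The first part stands: a reader might infer bias or an invalid test, and nothing supports that. The second stands only in part. The article does not leave the method open. It names the tests, the threshold, the software and the imputation package, and applies those tests to outcomes in general.

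Four further objections hold and limit the point:

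- The documents give no r. MRC grading needs voluntary contraction, and the article describes sedated patients. Baseline MRC may be at floor or missing in many of them, so the gain could be small.
- Testing at every time point is an inference. The outcome sections give measurement schedules and do not say that each day or month will be tested. Only secondary outcomes are affected; the primary has one post-baseline time, with its interim look under Pocock.
- The power illustration depends on reading 0.5 as a standardised mean difference. The stated total follows from the two proportions, so 60% should not be quoted as the trial's power.
- A reader might infer that the plan promises a mean difference that Mann–Whitney cannot supply. It promises only effect estimates with intervals, and a Hodges–Lehmann shift would meet that.

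**Conclusion.** The point holds as one of efficiency and of analyses left open to choice after the data are seen. The article fixes unadjusted tests, chosen on observed normality, for outcomes whose baseline values it already collects. The size of the loss rests on an assumed r: 9% to 49% of the variance for r from 0.3 to 0.7, and close to nothing if baseline MRC carries little information.

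For the repeated secondary outcomes, the stated method leaves room for up to 21 diaphragm comparisons. A reader might take 66% as the risk of a false diaphragm finding. That figure needs 21 independent tests, and also that all of them are carried out. With between-day correlations of 0.5 to 0.9 and the three measures independent, it is about 30% to 55%, and lower if the measures are also correlated. The change is worth making before the interim analysis, but nothing here invalidates the trial.

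**What to change.** Name one primary analysis in advance: day-7 MRC by ANCOVA, adjusted for baseline MRC and baseline APACHE II in all patients. Handle missing baseline MRC by one stated rule, either a missing-value indicator or the multiple imputation already planned, so that every patient is in the same model. Remove the choice of test on observed normality. Adjust each secondary score for its own baseline in the same way.

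For each diaphragm measure and for the Barthel Index, fit one baseline-adjusted repeated-measures model with one pre-stated contrast, for example day 7 for the diaphragm and month 6 for Barthel; treat other time points as descriptive. State that the diaphragm baseline is a reading taken before the first NMES session. State how deaths enter the Barthel analysis: the Introduction cites high mortality, and a repeated-measures model with no such rule implicitly carries scores past death.

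The cost is wording and slightly more analysis work, with no new patients, visits or measurements. The downside is reliance on model assumptions. If baseline turns out to predict little, the price is about one degree of freedom per covariate.

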### Safety assessment and monitoring

NMES intervention will be carried out strictly based on the instrument operation specifications and implemented by two physiotherapists who have completed operation training. Patients will be informed of the potential adverse events of NMES and sign an informed consent form. Adverse events may occur during treatment: mean arterial blood pressure < 65 mmHg, 40 bpm < heart rate < 130 bpm, SpO_2_ < 88%, skin redness, skin burns, skin blisters, pain, myocardial ischemia, and arrhythmia. The NMES group will complete NMES therapy under the supervision of a physiotherapist. During treatment, any patient discomfort will be dealt with immediately (reduce the intensity of electrical stimulation or stop the intervention). The research team will judge the severity of adverse events and analyze the correlation with the intervention. Patients who suffer harm or complications caused by the intervention will receive medical treatment at the Second Affiliated Hospital of Chongqing Medical University free of charge. All serious adverse events will be reported to the ethics committee within 48 h.

Based on the sequential study design, the primary outcome will be analyzed when 50% of participants (40 participants) have randomly enrolled to complete the intervention and data collection. An independent statistician who is blinded to the intervention process will be responsible for performing the data analysis. Type I error statistical analysis will be performed using the Pocock approach with *α* = 0.05. The interim analysis results will be reported to the data monitoring committee (DMC). The DMC will access all data and discuss to decide whether the trial should be continued, modified, or halted earlier than intended.

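### The Pocock interim look and the general P ≤ 0.05 rule give conflicting thresholds for the final test of the primary outcome

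*Protocol article*

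**What the plan says.** Three parts of the protocol article bear on this point.

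- **Data collection and statistical analysis.** This section names the tests for baseline characteristics and outcomes, promises 95% confidence intervals, and sets one threshold: P "values ≤ 0.05 will be considered significant". It makes no exception for the primary outcome or for an outcome already tested at an interim look.
- **Safety assessment and monitoring.** Under what it calls a sequential design, "the primary outcome will be analyzed when 50% of participants (40 participants) have randomly enrolled to complete the intervention and data collection". It continues: "Type I error statistical analysis will be performed using the Pocock approach with" α = 0.05. The result goes to the data monitoring committee, which may "decide whether the trial should be continued, modified, or halted earlier than intended". No nominal level is given for either look, and the final analysis is not mentioned.
- **Simple size** (the sample size section). The inputs are ICU-acquired weakness rates of 0.45 and 0.11, a 5% type I error and 90% power. From these "a sample size of 40 participants in each group was calculated". The section ends: "Allowing for a 20% loss to follow-up, this study was designed to include 80 cases". It does not mention an interim look.

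**The concern.** A Pocock design uses the same nominal level at every look, set below 0.05 so that the looks together cost 5%. The analysis section sets 0.05 for everything. Both rules cannot govern the final test of the primary outcome. For any final P between about 0.0294 and 0.05, one section calls the trial positive and the other does not.

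The only α printed in the monitoring section is also 0.05, so an analyst could easily carry that number to the final test in good faith. What is at stake is the rule that decides the trial's main conclusion, which should be unambiguous before the interim data are seen. A second, smaller matter is that the power statement appears to have been worked out without the interim look.

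**Working it through.** **Inputs.** From the protocol article: one interim at 40 of 80 participants (information fraction 0.5), Pocock, overall α = 0.05, final threshold 0.05, rates 0.45 and 0.11, 90% power, 20% loss, 1:1 allocation. Assumed: two-sided tests (sidedness is not stated), and an interim crossing that counts as a declaration of efficacy.

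**Step 1: the Pocock level.** Under no effect, the interim and final statistics Z₁ and Z₂ are standard normal with correlation √0.5 = 0.7071. Solve for c in

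1 − P(|Z₁| < c, |Z₂| < c) = 0.05.

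The solution is c = 2.178, a nominal two-sided P of 0.0294 at each look. This reproduces the protocol's stated 5% overall error.

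**Step 2: overall type I error under each reading.** The error is P(|Z₁| ≥ c₁) + P(|Z₁| < c₁, |Z₂| ≥ c₂).

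| Interim level | Final level | Overall error |
|---|---|---|
| 0.0294 | 0.0294 | 5.00% |
| 0.0294 | 0.05 | 0.0294 + 0.0380 = 6.74% |
| 0.05 | 0.05 | 0.0500 + 0.0331 = 8.31% |

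A simulation of 400,000 trials using t tests at 20 and then 40 per arm gave 5.02%, 6.74% and 8.31%. With the Lan-DeMets Pocock-type spending function, the interim level is 0.0310 and the final level that keeps 5% is 0.0277. Using 0.05 at the end instead gives 6.86%. The choice of Pocock variant hardly matters.

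**Step 3: the sample size.** The unpooled two-proportion formula is

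n = (1.960 + 1.282)² × (0.45×0.55 + 0.11×0.89) / 0.34² = 3.2415² × 0.3454 / 0.1156 = 31.4, so 32 per arm.

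Then 32 / 0.8 = 40 per arm, or 80 in total, which matches the protocol. The pooled formula gives 35 per arm (44 after loss), and the continuity-corrected formula gives 41 (52 after loss). The unpooled fixed-sample formula is thus the one that reproduces 40 per arm after the loss allowance at 90% power, and it leaves nothing for the interim look.

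**Step 4: power under Pocock.** A fixed-sample test with exactly 90% power has drift 3.2415 at the final look and 3.2415 × 0.7071 = 2.292 at the interim. With |Z| ≥ 2.178 at both looks, the probability of rejection is 87.0%. Rounding up to 32 per arm raises the drift to 0.34 / √(0.3454/32) = 3.273 and the power to 87.6%. If nobody is lost and all 40 per arm are analysed, the drift is 3.659 and the Pocock power is 93.8%. Restoring 90% at the evaluable number would need a drift of 3.400, that is (3.400/3.2415)² = 1.10 times the information.

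**The case against.** The strongest defence is that a specific rule overrides a general one. The monitoring section names a valid procedure for this very outcome, and Pocock covers both looks by definition. On that reading the 0.05 sentence serves the other comparisons and the error is 5.0%. This reading is reasonable, and it is why a reader who infers that the trial's type I error simply is inflated goes further than the text allows. It does not remove the conflict. The monitoring section never says that it governs the final test, gives no per-look level and repeats 0.05. The analysis section covers outcomes without exception, and a 95% interval would not match a test at 0.0294.

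Four further objections carry weight:

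- **Efficacy stopping is implied, not stated.** The section sits under safety, and the committee's options are general. Inflation arises only if an interim crossing counts as a positive result. Type I error control on the primary outcome has little purpose otherwise, but this remains an inference.
- **The 8.3% figure.** A reader might infer a range up to 8.3%. That needs an interim test at 0.05, which is not a Pocock look. It applies only if α = 0.05 is misread as a per-look level.
- **Detail left to an analysis plan.** Boundary tables and the form of adjusted intervals may stand in a plan that is not shown, so their absence is no fault. The point rests only on two statements made in this article.
- **Choice of boundary.** A reader might infer that Pocock is itself wrong and that O'Brien-Fleming is required. Nothing in the article supports this. Pocock is a legitimate choice, and replacing it would be a preference.

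**Conclusion.** The conflict is real and affects the primary conclusion: the article gives two thresholds, about 0.0294 and 0.05, for the same final test. The overall type I error is about 6.7% instead of 5% if three conditions hold: the interim can declare efficacy, it is run at the Pocock level, and the final primary test uses 0.05. Two-sided testing and a look at half the information are assumed.

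The documents do not show that the trial will run at 6.7%, only that one of their two stated rules leads there.

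On power, the 90% claim reproduces as a fixed-sample figure. It becomes about 87% under Pocock if the full 20% is lost, and stays above 90% if nobody is lost. Both figures rest on the ICU-acquired weakness rates used in the sample size section.

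**What to change.** - **Threshold.** In the analysis section, state that the primary outcome is tested at a nominal two-sided P ≤ 0.0294 at both the interim and the final analysis. Keep 0.05 for outcomes not tested at the interim.
- **Confidence interval.** For the primary outcome, report an interval consistent with that level (100% − 2.94% = 97.06% is the direct match) in place of the unqualified 95%.
- **Interim.** In the monitoring section, say that α = 0.05 is the overall level across both looks, and say whether a crossing at the interim may be declared as efficacy.
- **Power.** Restate it with the Pocock boundary: about 87% if the full 20% is lost.

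The cost is a few sentences, a slightly stricter final threshold and a slightly lower stated power. No added enrolment is required; about 10% more information would be needed only if the sponsor wishes to keep 90% after full loss.
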